### Static Two-Point Discrimination test (S2PD)

The primary outcome of this study is the return of sensation 12 months after nerve injury, assessed using the S2PD, measured in millimeters. S2PD is the most widely used test to evaluate sensory function in the fingers [7]. The S2PD test evaluates tactile spatial acuity i.e. the ability to distinguish between two separate points of contact on the skin. The S2PD test, initially described by Weber in 1834, and later modified by Moberg [7] is performed using the Mackinnon-Dellon Disk-Criminator™ by applying two pins longitudinally over the radial and ulnar sides of the fingertip, with distances ranging from 0 to 25 mm. The minimum distance at which an individual can accurately distinguish between one or two points is recorded as the S2PD value. The test will be conducted in a standardized manner, ensuring that the pins are applied with just enough pressure to cause skin blanching [8], as excessive force may stimulate other receptors rather than mechanoreceptors responsible for pressure sensation [9, 10]. The injured finger is examined, as well as the corresponding finger on the uninjured hand for comparison. A correct response in seven out of ten random applications is required for a valid measurement.

Classification of sensory recovery according to the Mackinnon-Dellon scale [11], modified from the Highet classification, will be used. Sensation is classified as: Poor = >15 mm, Good = 7–15 mm, Excellent = 2–6 mm. The test and its validity have been questioned [12, 13].

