### Participant timeline {13}

#### Sample size {14}

This study was designed as a prospective superiority trial, aiming to determine whether one treatment strategy resulted in a superior sensory recovery outcome compared to the other. The primary endpoint was the proportion of participants achieving recovery of sensibility, defined as S2PD ≤ 10 mm, measured at the 1-year follow-up.

A power calculation was performed based on the assumption of a 20% clinically meaningful difference between groups. Using a two-sided significance level of *p* < 0.05 and a statistical power of 80%, the required sample size was calculated to be 150 patients. This calculation was based on an expected outcome proportion derived from a previously published study [38]. To account for an anticipated dropout rate of 10%, the total sample size was adjusted to 166 participants.

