## Statistical methods

### Statistical methods for primary and secondary outcomes {20a}

Primary outcome is a dichotomous outcome that will be presented as proportions of patients obtaining return of 2PD < 10 mm 1 year after injury, presented with 95% confidence interval, and proportions between groups will be compared with Chi^2^ analysis.

All numerical values will be tested for normality by Shapiro–Wilk’s test.

We assume normality/parametric data for age, AROM, and grip strength. Results are presented as numerical values on an interval scale. Central tendencies of data will be described as means with their corresponding standard deviation, and comparisons between groups will be performed with Student’s *t*-test or repeated measures ANOVA.

Categorical data will be presented as proportions and compared by Chi^2^ analysis, unless Fisher’s exact test is demanded due to expected small numbers. Ordinal data will be presented as medians and interquartile range (IQR), and Mann–Whitney *U*-tests or Wilcoxon’s test used for comparisons between groups.

We assume a skewed distribution for time to injury, sick leave, and PROMs, which will be presented as medians with IQRs and compared by Mann–Whitney *U*-tests or Wilcoxon’s test.

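### The primary responder cut is S2PD ≤ 10 mm in the sample-size section but < 10 mm in the primary analysis, so a reading of exactly 10 mm has no settled classification

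*Protocol article*

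**What the plan says.** Protocol article, Sample size {14}: the primary endpoint is the proportion of participants who recover sensibility, "defined as S2PD ≤ 10 mm, measured at the 1-year follow-up". The calculation rests on the "assumption of a 20% clinically meaningful difference between groups", a two-sided 5% level and 80% power, and gives 150 patients (166 after allowance for dropout). The base rate is not printed: "This calculation was based on an expected outcome proportion derived from a previously published study".

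Protocol article, Statistical methods for primary and secondary outcomes {20a}: the primary outcome is dichotomous, the "proportions of patients obtaining return of 2PD < 10 mm 1 year after injury", compared between groups by chi-square.

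Protocol article, Static Two-Point Discrimination test (S2PD): the outcome is recorded in millimetres, "with distances ranging from 0 to 25 mm", and "The minimum distance at which an individual can accurately distinguish between one or two points is recorded as the S2PD value". Results are also to be classified as "Poor = >15 mm, Good = 7–15 mm, Excellent = 2–6 mm". This section has no 10 mm cut.

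The abstract and the objectives name S2PD without a threshold. Both 10 mm statements are current text; the Trial status section calls this the first version of the protocol.

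**The concern.** The two sections describe the same yes/no outcome at the same time point and differ only at 10 mm, which lies within the stated range of the test. An analyst who follows {20a} tests a stricter endpoint than the one behind the 150 patients. The success rates, and possibly the significance of the primary result, then depend on which section is followed.

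Timing adds to this. Patients and staff are unblinded, there is no data monitoring committee, and recruitment began on 29 August 2022, so one-year readings have been falling due since late August 2023. If the discrepancy is settled late, it could be settled by people who know how the 10 mm readings fall by arm. The Discussion counts an outcome defined in advance, and protection against selective reporting, among the trial's strengths. Two definitions weaken that claim.

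**Working it through.** **1. The text.** Classification of a recorded value under each rule:

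| S2PD reading | Sample size {14}: ≤ 10 mm | Analysis {20a}: < 10 mm |
|---|---|---|
| 9 mm | success | success |
| 10 mm | success | failure |
| 11 mm | failure | failure |

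No other section settles the middle row. On the three-band scale 10 mm falls inside the 7–15 mm class, so the bands do not decide it. The contradiction needs no arithmetic; the steps below only size it.

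**2. The plan's 150.** Inputs from the document: two-sided α = 0.05, power 80%, 1:1 allocation, a 20% difference (read as 20 percentage points). The base proportion is not stated, so 150 cannot be reproduced from the document alone. With n per arm = [1.96·√(2p̄(1−p̄)) + 0.8416·√(p₁(1−p₁) + p₂(1−p₂))]² / (p₁−p₂)², the total runs from 70 to 194 depending on the base rate. The pair 64% vs 84% (p̄ = 0.74) gives (1.2158 + 0.5083)² / 0.04 = 74.3, so 75 per arm and 150 in total, with power 80.4%. That pair is my working assumption for the ≤ 10 mm rule.

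**3. How many readings might be exactly 10 mm.** Assumptions, none from the documents: whole-millimetre readings, roughly normal, SD s of 2.5 or 5 mm. Then mean = 10.5 − z(p)·s, P(≤ 9) = Φ((9.5 − mean)/s), and the share at 10 mm is p − P(≤ 9).

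| s | p at ≤ 10 | Mean (mm) | p at < 10 | Share at 10 mm |
|---|---|---|---|---|
| 2.5 | 84% | 8.01 | 72.4% | 11.6% |
| 2.5 | 64% | 9.60 | 48.3% | 15.7% |
| 5 | 84% | 5.53 | 78.7% | 5.3% |
| 5 | 64% | 8.71 | 56.3% | 7.7% |

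Participants changing class, both arms: 75 × (0.116 + 0.157) = 20.5 for s = 2.5, and 75 × (0.053 + 0.077) = 9.8 for s = 5.

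**4. Between-arm difference and power.** In this model the < 10 mm difference is 72.4 − 48.3 = 24.0 points (s = 2.5; unrounded rates) or 78.7 − 56.3 = 22.4 points (s = 5), against 20 under ≤ 10 mm. Power with 75 per arm is 86% or 84%.

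Under a different assumption, an equal share at exactly 10 mm in each arm, the difference stays at 20 points but both rates move towards 50%:

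| Share at 10 mm, each arm | Rates at < 10 mm | N for 80% power | Power with 75 per arm |
|---|---|---|---|
| 2% | 62% vs 82% | 156 | 78.5% |
| 5% | 59% vs 79% | 166 | 76.0% |
| 10% | 54% vs 74% | 180 | 72.7% |

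So even the sign of the power change depends on the assumption.

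**5. Type I error.** I simulated trials with 75 per arm and no true difference (common success rates of 64%, 74% and 84%, same normal model, chi-square test without continuity correction). Either rule alone rejects in about 5–6% of trials. Reporting whichever of the two is significant rejects in about 7–9%.

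**The case against.** The strongest reply is that a one-character difference between otherwise matching definitions is a drafting slip, that few participants may read exactly 10 mm, and that a separate analysis plan may already have chosen one rule. It probably is a slip, and the affected share is unknown. But a separate plan would have to depart from one of the two published definitions, and the article would still contradict itself on its primary endpoint.

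The model is also weak. At SD 5 mm and 84% success the implied mean is 5.5 mm, and Φ((0.5 − 5.53)/5) = 15.7% of that arm would round to 0 mm or below. The low end of the 10–20 range therefore comes from an implausible distribution. That stands, and it is why the figures are only illustrative.

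A reader might infer three stronger points, which the documents do not support:

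- *That the Mackinnon-Dellon bands are a third, conflicting primary definition.* A 12 mm reading is Good on the scale and a failure on the binary endpoint, but a descriptive three-band scale and a binary cut can coexist. The article never makes the bands the primary analysis.
- *That 10–20 reclassified participants swamp the target difference of 15 per arm* (20% of 75). The first figure is a total over both arms, all moving from success to failure; the second is a between-arm contrast. In the same model the contrast shifts by only 2.4–4.0 points, roughly 2–3 participants per 75.
- *That the discrepancy in itself costs power or inflates type I error.* Power can move either way, and the inflation requires the cut to be chosen after both results are known.

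**Conclusion.** Wrong as written. The sized endpoint and the analysed endpoint differ at 10 mm, and nothing in the article reconciles them. This finding rests on the text and on 10 mm being a value the test can return.

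Its numerical effect cannot be fixed from the documents, because neither the share reading exactly 10 mm nor the base proportion is given. The figures of 10–20 of 150 participants reclassified, and of power between about 73% and 86%, hold only under the assumptions shown. Type I error is a concern only while the choice stays open.

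The point matters because this is the primary endpoint of an unblinded trial already recruiting, and because the correction is nearly free. It does not show that the trial is underpowered.

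**What to change.** State one identical cut in Sample size {14} and Statistical methods {20a}, and repeat it in the S2PD outcome definition. The natural default is ≤ 10 mm, since that is the endpoint given for the sample size. First check which cut the cited source of the expected proportion used: if it used < 10 mm, the sample-size statement is the one that needs attention.

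Date and document the correction before any 12-month comparison by arm. Labelling the Mackinnon-Dellon classes as a descriptive presentation is an optional clarification.

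Cost: a one-line correction carried through three sections, with no extra patients, visits or data.

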## Objectives {7}

The primary objective of this study is to investigate whether the return of static two-point discrimination (S2PD) after non-operative treatment is inferior to surgical repair of isolated digital nerve injury at 1-year follow-up.

Secondary objectives include comparison between the two groups for differences in patient-reported outcomes and hand function, including range of motion, grip strength, and additional aspects of sensation. We will also investigate complications and sick leave.

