### Intervention description {11a}

At first examination, eligibility criteria, demographics, and information regarding the injury and its extent (perceived gender, date of birth, smoking, dominant hand, injured hand, profession, date of injury, injury mechanism, injured finger, injured nerve (ulnar/radial), level of injury (proximal or middle phalanx)) will be registered. Clinical examination will include sensory evaluation with S2PD of both the injured and the contralateral finger, as well as measurement of the distance between the injury and the fingertip in millimeters. Participants will be randomized to either nerve repair and cast or cast immobilization alone.

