### Methods for additional analyses (e.g. subgroup analyses) {20b}

The primary outcome will be analyzed with mixed models effects, taking possible confounders into account, such as age (years), gender (female/male), smoking (yes/no), handedness (left/right), injury mechanism, level of injury (proximal/middle phalanx), distance from injury to fingertip (mm), time from injury to operation/immobilization (days). No other additional or subgroup analyses are planned.

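### The primary chi-square is valid, but the plan names no between-arm difference with a confidence interval and leaves entry S2PD out of its named covariates

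*Protocol article*

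**What the plan says.** All references are to the protocol article.

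- **Objectives {7}**: the question is whether S2PD after "non-operative treatment is inferior to surgical repair of isolated digital nerve injury at 1-year follow-up".
- **Static Two-Point Discrimination test (S2PD)**: the primary outcome is return of sensation at 12 months, "assessed using the S2PD, measured in millimeters". The matching finger of the uninjured hand is also examined.
- **Sample size {14}**: "The primary endpoint was the proportion of participants achieving recovery of sensibility, defined as S2PD ≤ 10 mm". The basis is a 20% difference, two-sided 5% significance and 80% power, giving 150 patients, or 166 with 10% dropout.
- **Statistical methods {20a}**: the endpoint is set out here as "Primary outcome is a dichotomous outcome that will be presented as proportions of patients obtaining return of 2PD < 10 mm 1 year after injury". The same sentence gives those proportions a 95% CI, and for the test it says "and proportions between groups will be compared with Chi^2^ analysis".
- **Additional analyses {20b}**: the primary outcome is also to be analysed by mixed-effects modelling, "taking possible confounders into account, such as age (years), gender (female/male), smoking (yes/no" and so on. The other named covariates are handedness, injury mechanism, level of injury, distance from injury to fingertip, and time to treatment.
- **Intervention description {11a}**: at the first examination, "Clinical examination will include sensory evaluation with S2PD of both the injured and the contralateral finger". Table 1 also lists S2PD at allocation and at 3 weeks, 3, 6 and 12 months.

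**The concern.** The objective is directional and the design names a difference that matters, so the natural primary result is the difference between arms with its interval. As written, the comparison yields a p-value, and the intervals belong to the two proportions separately. Neither shows directly whether a 20-point deficit for cast alone has been excluded. A non-significant result could then be taken as evidence that omitting surgery is safe for sensation when the data do not show that.

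The second issue is unused baseline information. S2PD at entry is measured on both the injured and the matching uninjured finger, yet neither value enters the primary comparison or appears among the named covariates of the additional model. A baseline measurement of the outcome variable is usually the first candidate for adjustment. This matters more where patients are hard to recruit: the section on protocol amendments reports a low inclusion rate and a requested extension of the end date.

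**Working it through.** **1. The plan's sample size.** The event rate is not stated, so it must be assumed, with the 20% read as absolute points. With pooled variance,

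n per arm = [1.96·√(2p̄q̄) + 0.842·√(p₁q₁ + p₂q₂)]² / (p₂ − p₁)².

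For 64% v 84%: p̄ = 0.74, √(2·0.74·0.26) = 0.620, √(0.2304 + 0.1344) = 0.604. This gives (1.216 + 0.508)² / 0.04 = 74.3, so 75 per arm and 150 in total. The pair 16% v 36% gives the same total. Mid-range rates need more (40% v 60%: 194). The stated 150 is attainable, and the chi-square is the test it was sized for.

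**2. Precision of the risk difference at 75 per arm.** Half-width = 1.96·√[(p₁q₁ + p₂q₂)/75].

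| Proportions | Half-width |
|---|---|
| 64% v 84% | 1.96·√(0.3648/75) = 13.7 points |
| 40% v 60% | 1.96·√(0.48/75) = 15.7 points |
| 50% v 50% | 1.96·√(0.50/75) = 16.0 points |

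**3. Why the difference is needed.** Two invented results, repair v cast, both non-significant by chi-square:

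| Recovered | Difference | 95% CI | p |
|---|---|---|---|
| 60/75 v 53/75 | 9.3 points | −4.4 to 23.0 | 0.19 |
| 57/75 v 54/75 | 4.0 points | −10.0 to 18.0 | 0.58 |

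The first leaves a 20-point deficit for cast possible; the second excludes it. The verdict of non-significance is the same. With a true 10-point deficit, exact chi-square power at 75 per arm is 0.25–0.29 for lower rates of 40–70%, so 71–75% of such trials would be non-significant.

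**4. Gain from adjusting for a baseline S2PD value.** Simulation with 75 per arm, 64% v 84%, 3,000 trials per setting, a normal latent S2PD and one baseline covariate. The correlation is assumed; the documents give none.

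| Analysis of the binary endpoint | r = 0.3 | r = 0.5 |
|---|---|---|
| Unadjusted chi-square | 81% | 80% |
| Logistic regression, treatment coefficient | 83% | 85% |
| Logistic regression, standardised risk difference | 83% | 86% |

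**5. What an analysis in mm could add.** This depends wholly on how treatment acts, again at 64% v 84% and 75 per arm.

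| Assumed mechanism | Chi-square | Rank test on mm |
|---|---|---|
| Whole distribution shifts (latent shift 0.64 SD) | about 81% | about 96% |
| Only the proportion recovering changes (recovered 4–10 mm, others 11–25 mm, same spread in both arms) | about 81% | about 57% |

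The ordering reverses between the two mechanisms, and the documents do not say which applies.

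**The case against.** The other side has a good deal right. A chi-square on a pre-specified binary endpoint is a valid test and agrees with the sample-size basis. The design is declared a superiority trial, and nowhere does the text say that a non-significant result will be read as showing that cast is not inferior. A difference in proportions and its interval can be worked out from the two reported proportions. The choice of effect measure is often left to an analysis plan, which is not shown here. Section {20b} already plans an adjusted model of the primary outcome, includes age and level of injury, and keeps its covariate list open.

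Three stronger readings are tempting and do not hold:

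- A reader might infer that the mm values are discarded. The text does not establish this. The additional model is of the primary outcome, which one section describes in mm and another as dichotomous, so the scale is unclear rather than known to be binary.
- A reader might infer that dichotomising wastes about 15 points of power. The 96% figure requires a shift of the whole distribution; if treatment changes only who recovers, the rank test does worse than the chi-square.
- A reader might infer that the lack of an S2PD threshold for entry lets participants already at 10 mm or better count as recovered. No frequency is available, a nerve laceration is required for entry, and this is a side issue to the analysis.

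What remains is that section {20a} does fix the form of the primary comparison and gives the interval to the proportions, and no named analysis uses entry or contralateral S2PD.

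**Conclusion.** The point holds as a matter of estimation and efficiency, not of validity. The primary result should be a between-arm difference with an interval, because the objective and the 20% difference can be judged only on that scale. Expected precision is about 14 to 16 points either side at 75 per arm, for the rates shown.

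The power gain from adjustment is modest: about 81% to 83–86% at assumed correlations of 0.3–0.5, and less if the true correlation is lower. It needs no new data. The 96% rank-test figure should not be claimed.

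It would also go too far to call a null result uninterpretable, since the interval can be derived from the reported proportions, or to say the end date has already been extended, since the protocol reports only that an extension was requested. The conclusions rest on an undisclosed event rate, on reading the 20% as absolute points, and on a normal latent S2PD.

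**What to change.** 1. Keep the binary endpoint and its sample-size basis. Use one cut-point throughout: the sample-size section includes exactly 10 mm and the statistical methods exclude it.
2. Make the primary estimate the between-arm risk difference with 95% CI, from logistic regression with standardisation. Adjust for contralateral-finger and injured-finger S2PD at entry plus a short fixed list such as age and level of injury.
3. State that the interval is read against 20 points, and that p > 0.05 will not be read as showing that non-operative treatment is not inferior.
4. State whether the mixed model in section {20b} analyses the binary outcome or S2PD in mm.
5. Add one supportive rank or ordinal analysis of 12-month S2PD in mm, with no discrimination at 25 mm as the worst rank.

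The cost is wording only, with no extra visits or measurements. The one downside is that the primary analysis becomes slightly less simple than a 2×2 table; the unadjusted chi-square can still be reported beside it.

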### The HAKIR-8 questionnaire (HQ-8)

The HQ-8 questionnaire was constructed for evaluating patient-reported outcomes after hand surgery [29] and has been used since 2010 [17]. The HQ-8 includes seven questions concerning perceived symptoms in the affected or injured hand (pain on load, pain in motion without load, pain at rest, stiffness, weakness, numbness, and cold sensitivity) and one item about the ability to perform daily activities. Items are scored on a numeric 11-point box scale (NRS11) with numerical descriptors (0, 10, 20,…0.100) indicating no or maximal symptoms. The preoperative and the postoperative questionnaires are identical, with the exception that a question about the satisfaction with the result, scored 0–100, is added postoperatively. The questionnaire was adapted for the study by adding a “Not Relevant” option to the question regarding the “operated hand,” since not all patients will be operated. Its validity has been studied and is shown to be useful as a complement to Quick-DASH after hand surgery [29].

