### Cold intolerance

In the DN4 questionnaire, the first question (1:2) addresses cold and pain, and so does question number 7 in the HQ-8 questionnaire. The results from these questions will be analyzed separately from the rest of the questionnaires in order to assess cold intolerance. Cold intolerance is the most common complication after digital nerve injury [37].

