## Data collection and management

### Plans for assessment and collection of outcomes {18a}

Data will be collected at inclusion and during follow-up visits at 0–4 days, 3 weeks, 3, 6, and 12 months from injury (Table 1). At the time of inclusion, written informed consent will be obtained, and the inclusion protocol, including inclusion and exclusion criteria as well as demographic data (age, gender, smoking habits, handedness, occupation, comorbidities, injury mechanism, level of injury, injured hand, injured finger, injured nerve, distance from injury to fingertip, and time from injury to treatment), will be completed. After consenting to participate, randomization will be carried out, and PROMs (Quick-DASH, HADS, HQ-8 (before operation), PCS) will be filled out. Sensory relearning is offered 0–4 days after injury. At 3 weeks, the cast and sutures will be removed by a nurse before seeing the occupational therapist. At follow-up visits, the investigating occupational therapist uses the follow-up study protocol for assessments (S2PD, AROM, SWM, Mini Sollerman test, Temperature sensation, Sharp/Dull, Grip strength + VAS, Pinch grip + VAS) and PROMs (Quick-DSAH, HQ-8 after operation/treatment, DN4), to make sure that all measurements and forms are completed.

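### Quick-DASH and HQ-8 are measured at inclusion, but the inclusion scores are not used as covariates in the arm comparisons, which costs precision on secondary outcomes

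*Protocol article*

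**What the plan says.** All references are to the protocol article.

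- **Collection.** Table 1 schedules Quick-DASH and HQ-8 in the allocation column and again at 3, 6 and 12 months. Section {18a} gives the order at inclusion: "After consenting to participate, randomization will be carried out, and PROMs (Quick-DASH, HADS, HQ-8 (before operation), PCS) will be filled out".
- **Same instrument.** The HQ-8 section states: "The preoperative and the postoperative questionnaires are identical, with the exception that a question about the satisfaction with the result" is added afterwards. Each follow-up symptom item thus has a matching inclusion item.
- **Analysis.** Section {20a} states: "We assume a skewed distribution for time to injury, sick leave, and PROMs, which will be presented as medians with IQRs". The same sentence fixes the comparison: "PROMs, which will be presented as medians with IQRs and compared by Mann–Whitney" U-tests or Wilcoxon's test. It gives the inclusion score no role.
- **Adjustment.** Section {20b} states: "The primary outcome will be analyzed with mixed models effects, taking possible confounders into account". Its example covariates include no questionnaire score, and it closes with: "No other additional or subgroup analyses are planned".
- **Cold intolerance.** This is assessed from a DN4 item and an HQ-8 item ("so does question number 7 in the HQ-8 questionnaire"). The section does not mention the HQ-8 inclusion value. DN4 is first collected at 3 weeks.

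**The concern.** When a questionnaire score is both a baseline measurement and a later outcome, its baseline value is usually among the better predictors of the outcome. A rank test on follow-up scores alone leaves that predictable variation in the error. It also leaves any chance difference between arms at inclusion in the result.

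Patient-reported outcomes are among the secondary objectives in section {7}. The section on protocol amendments reports a low inclusion rate, so precision that needs no extra patients is worth having. At stake is the sharpness of the Quick-DASH and HQ-8 comparisons, including HQ-8 item 7 on cold sensitivity. The primary outcome is not affected.

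**Working it through.** **Plan's own figure.** There is none to reproduce. The 150 evaluable patients in section {14} are for the binary S2PD outcome; no SD, power or sample size is given for any questionnaire.

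**Inputs.** From section {14}: 150 / 2 = 75 per arm, two-sided 5%, 80% power. Assumed, because the article does not give it: the correlation r between inclusion and follow-up scores.

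**Step 1: formulas.** Adjusting for a covariate with correlation r multiplies residual variance by 1 − r². The difference detectable with 80% power, in SD units, is (1.960 + 0.842) × √(2/75) × √(1 − r²). Without adjustment this is 2.802 × 0.1633 = 0.457 SD. The sample size that would give the same precision unadjusted is 75 / (1 − r²) per arm.

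| r | 1 − r² | Detectable difference (SD) | Power at 0.457 SD | Equivalent n per arm |
|---|---|---|---|---|
| 0 | 1.00 | 0.457 | 80.0% | 75 |
| 0.1 | 0.99 | 0.455 | 80.4% | 76 |
| 0.2 | 0.96 | 0.448 | 81.6% | 78 |
| 0.3 | 0.91 | 0.436 | 83.6% | 82 |
| 0.5 | 0.75 | 0.396 | 89.9% | 100 |
| 0.7 | 0.51 | 0.327 | 97.5% | 147 |

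**Step 2: skewed scores and rank methods.** Two simulations used 75 per arm and a skewed 0–100 score. Simulation A used beta-shaped scores, a latent shift of 0.46 SD and 3000 runs per setting. Simulation B used a log-normal shape with a floor at 0, a shift of 0.47 SD and 2000 runs. Each cell shows power for Mann–Whitney, then for rank analysis of covariance.

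| r | A | B |
|---|---|---|
| 0.1 | – | 80% → 80% |
| 0.2 | 77% → 78% | – |
| 0.3 | 78% → 81% | 78% → 82% |
| 0.5 | 79% → 88% | 80% → 90% |
| 0.7 | – | 78% → 96% |

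**Step 3: validity without adjustment.** With no treatment effect, rejection rates were 4.4–5.4% in A and 4.3–4.9% in B. The loss is precision, not error control.

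**Step 4: is the gain needed for a large effect?** The Quick-DASH section reports a minimal important difference of 15–20 points. Take 15 points, 75 per arm and an assumed SD, divided by √0.955 for the efficiency of the rank test under normality:

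- SD 20: standardized difference 15 / (20.47 × 0.1633) = 4.49, so power is Φ(4.49 − 1.96) = 99.4%.
- SD 25: 15 / (25.58 × 0.1633) = 3.59, so power is Φ(3.59 − 1.96) = 94.8%.

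A Quick-DASH effect of that size would be found without adjustment. The gain matters for smaller differences.

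**Step 5: risk in adjusting as the forms are now ordered.** Suppose there is no treatment effect, but knowing the allocation shifts the inclusion score by 0.3 SD (assumption). In B, the adjusted test then rejects in about 5% of trials at r = 0.1, 9% at 0.3, 16% at 0.5 and 35% at 0.7. The unadjusted test stays at 4.7–5.9%.

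**The case against.** **The randomized comparison is sound without adjustment.** This stands. The case for change rests on precision and chance imbalance alone.

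**The gain is assumed.** This stands in part. The article gives no correlation, and a score taken within days of a laceration may predict the 12-month state poorly. At r = 0.1–0.2 the gain is about one percentage point or less in simulation. At 0.3–0.5 it is not trivial.

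**Adjustment could do harm.** This stands and shapes the fix. Section {18a} lists the forms after randomization, the trial is unblinded, and Table 1 puts both in one column. Recruitment began in August 2022, so new wording cannot reorder forms already completed.

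**The text may leave room.** Section {20a} does not say whether raw scores or changes are compared, and the closing sentence of {20b} may not govern {20a}. Even so, {20a} names the tests, and neither takes a covariate. If change was meant, its variance with equal SDs is 2(1 − r) times that of the raw score: 1.6 at r = 0.2, 1.4 at 0.3 and 1.0 at 0.5, against 0.96, 0.91 and 0.75 with adjustment.

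**A stronger reading is tempting.** A reader might infer that cold sensitivity present before the injury is counted as a complication of it. The documents do not support this. The inclusion forms are completed after the injury, examination may be up to 7 days later, and no pre-injury recall period is stated. The HQ-8 label refers to the operation, not the injury. The cold-intolerance section sets no cut-off and so defines no complication rate. DN4 has no inclusion value to adjust for.

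**Conclusion.** The concern holds as a point about precision. Quick-DASH and HQ-8 inclusion scores are collected, the named tests cannot use them as covariates, and planned adjustment is confined to the primary outcome.

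With 75 per arm, adjustment would be worth about 3, 7 and 25 extra patients per arm at r = 0.2, 0.3 and 0.5 (78, 82 and 100 against 75). These figures rest on the assumed r and on forms completed before the allocation is known.

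The documents do not show bias in the comparison by allocated arm, where earlier symptoms balance in expectation. That argument does not cover the as-treated analysis that section {20c} plans for complications, under which cold intolerance is listed. Only secondary outcomes are affected, so the change is worth making but does not decide the trial.

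**What to change.** 1. In section {18a} and Table 1, have Quick-DASH and HQ-8 completed at inclusion before the envelope is opened.
2. In section {20a}, compare arms at 12 months on Quick-DASH and on each HQ-8 item, including item 7, by rank analysis of covariance or a proportional-odds model. Use the inclusion score of the same measure as covariate.
3. For patients already enrolled, establish whether the forms preceded knowledge of the allocation. Where they did not, or this is unknown, keep the unadjusted rank test as the main analysis and report the adjusted one as a sensitivity analysis. Settle this before follow-up scores are compared by arm.

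The cost is a small change in the order of the inclusion visit, a check of existing records and some extra analysis. Because section {20c} excludes imputation, a patient without an inclusion form would drop out of the adjusted model. If the correlation proves low, little is gained.
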